Despite the advances in diagnosis and treatment of SAH, effective therapeutic interventions are still limited and clinical outcomes remain disappointing [1]. In addition to the early brain injury caused by the haemorrhage and inflammatory response to it, about one third of the patients with SAH develop delayed cerebral ischaemia (DCI) [3]. DCI is a primary contributor to persistent neurological impairment in patients with SAH [4–6]. DCI often results from vasospasms of proximal cerebral arteries and the microcirculation; however, there might be also other factors contributing to impaired cerebral perfusion and subsequently ischaemic injury, such as seizures, impaired autoregulation with reduction of regional blood flow, microthrombosis, spreading depolarisations, or high intracranial pressures [7]. Yet, approximately half of the patients with angiographic vasospasms progress to develop DCI, and spasms in small vessels may not be detected through standard angiography [5]. The pathophysiology underlying vasospasms, a primary driver of secondary brain injuries, remains incompletely understood; however, evidence suggests that oxidative stress, inflammation in response to haemorrhage, decrease of NO as well as episodes of hyponatraemia contribute to alterations in cerebral arterial diameter [8]. The latter is a common phenomenon in patients with SAH and occurs in 30 to 50% of the patients [9]. Although the only guideline-recommended strategies for reducing DCI include enteral nimodipine administration and the prevention of hypovolaemia and hypotension, primarily through fluid administration, there are currently no specific recommendations regarding the choice of crystalloid fluids for this patient population [10, 11]. Of note, patients with SAH often require several litres of intravenous fluid per day in order to counterbalance overt fluid losses and maintain adequate blood pressure. In a recent meta-analysis, Zampieri and colleagues summarise the current evidence on balanced versus normal saline infusion in critical care [12]. The study indicates a potential survival benefit associated with the use of balanced fluids in the general critical care population [12]. However, the meta-analysis also reveals that the administration of balanced fluids in patients with traumatic brain injury is associated with increased mortality [12]. This finding is consistent with other research suggesting that neuro-intensive care patients may benefit from a higher sodium load [3, 8, 11–13]. Similar might be true for patients with non-traumatic SAH. However, according to the guidelines by the ESICM, no prospective randomised trial has ever evaluated whether the type of infusion fluid used in patients with SAH might influence the incidence of vasospasms, and mortality and morbidity in these patients, and further investigations are highly warranted [11].

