
### Objectives {7}

#### Hypothesis

We hypothesise that the use of a sodium-enriched solution (0.9% saline) for fluid therapy in patients with non-traumatic SAH will result in a lesser occurrence of clinically significant vasospasm requiring immediate intervention than after treatment with a balanced, formally hypotonic infusion solution (Ringer’s lactate).

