### Eligibility criteria {10}

#### Inclusion criteria

All adult patients suffering from non-traumatic SAH and admitted to the Intensive Care Unit (ICU) or Intermediate Care Unit of one of the study centres are eligible for inclusion.

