#### Secondary endpoints

Secondary endpoints entail ICU and in-hospital mortality and 90-day mortality (aggregated as proportions of patients), treatment modalities for vasospasms (conservative vs. endovascular treatment—proportion of patients, number of days), need for decompressive hemicraniectomy (proportion of patients), evidence of brain oedema requiring intervention (proportion of patients), occurrence of hyper- or hyponatraemia (proportion of patients and number of days with hyper- or hyponatraemia), length of ICU and hospital stay (days), and neurological outcome at day 90 (ordinal scale) (see also Table 1).

**Table 1 Tab1:** Outcomes

Primary endpoint	Occurrence of clinically relevant vasospasm requiring immediate intervention during ICU/IMC stay
Secondary endpoints	
Mortality	ICU- and in-hospital mortality 90-day mortality
Length of stay	Length of ICU/IMC stay Length of hospital stay
Treatment modalities for vasospasms	Vasospasms requiring endovascular treatment Vasospasms managed conservatively
Brain oedema	Requiring any of the following: - Deep sedation - Ventricular drainage - Hyperventilation - Osmotherapy - Decompressive craniectomy
Electrolytes	Occurrence of hyponatraemia Occurrence of hypernatraemia
Neurological outcome at 90 days	Assessed by: - Modified Rankin Scale - Glasgow Outcome Scale Extended - Mini Montreal Cognitive Assessment

*ICU *Intensive Care Unit, *IMC *Intermediate Care Unit

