### Participant timeline {13}

All eligible patients will be randomised within 24 h of diagnosis (time stamp on first computed tomography or MRI). From randomisation up to discharge from ICU/IMC or day 14 after randomisation, whichever comes first, the patient will receive the allocated study fluids only. Fluid, water, and electrolyte balance will be assessed daily. Serum osmolality and urinary sampling will be performed at hospital admission (day 1) and on days 3, 7, 10, at day 14, or at the day of ICU/IMC discharge, whichever comes first. In addition, blood gas analysis including electrolytes will be performed at a minimum of once a day as long as the patient is in ICU/IMC. In addition, an electrocardiogram and, at the lead centre (University Hospital Bern, Inselspital), bioimpedance measures will be performed on predefined study days (see Table 2 [SPIRIT figure]).

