## Statistical methods

### Statistical methods for primary and secondary outcomes {20a}

This is a parallel group study. All randomised patients receiving the study fluid will be included in the primary analysis according to a modified intention-to-treat (mITT) principle [38]. The analysis is defined as modified because patients in whom an AV-malformation is subsequently identified as the source of the haemorrhage will be excluded, since this underlying condition falls outside the intended study population; their data will contribute only to a drop-out analysis. Normal distribution of continuous variables will be tested with the Shapiro–Wilk test. Normally distributed variables are presented with mean and standard deviation. Skewed or interval and ordinal variables are presented as medians with interquartile ranges. Normally distributed interval and ordinal variables will be compared by unpaired *t*-test and skewed variables by the Wilcoxon rank sum test. Comparisons of categorical variables were performed using chi-square test or Fisher’s exact test, as appropriate [39].

Whether the use of normal saline significantly influences our primary endpoint will be assessed by a logistic regression analysis adjusted for the stratification variables (trial site) in the ITT population [40]. For the primary endpoint, deceased patients or patients who were transferred prior to reaching the primary endpoint will be counted as “no event”. A sensitivity analysis with a modified primary endpoint will be used, defined as a composite endpoint of (i) clinically relevant vasospasms during the first 14 days, (ii) ICU/IMC readmission during the 14 days (if discharged earlier) because of vasospasms, or (iii) death within 14 days.

Our secondary endpoints will be assessed by logistic (binary endpoints) as well as linear regression models (such as mRS, GOSE, and miniMOCA) adjusted for the stratification variable (trial site).

We will report absolute risk difference and relative risk ratios with 95% CIs for dichotomous secondary outcomes. For continuous secondary outcomes, we will report mean differences with 95% CIs. Missing values will be imputed with the use of the last-observation-carried-forward method for measurements made after baseline. *P* values smaller than 0.05 are considered statistically significant. Secondary outcomes will be analysed in an explorative way.

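### The models for the hypo- and hypernatraemia endpoints adjust for trial site only, although a sodium value from before study fluid should usually be on file; adding it would recover some power on these exploratory endpoints

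*Protocol article*

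**What the plan says.** The section on statistical methods for primary and secondary outcomes {20a} sets one covariate rule for all secondary endpoints: "Our secondary endpoints will be assessed by logistic (binary endpoints) as well as linear regression models (such as mRS, GOSE, and miniMOCA) adjusted for the" (the only factor then named is trial site). No baseline value of any outcome is named. The same section describes the secondary analyses as exploratory.

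The sodium endpoints appear under Secondary endpoints as "occurrence of hyper- or hyponatraemia (proportion of patients and number of days with hyper- or hyponatraemia"; Table 1 lists hyponatraemia and hypernatraemia on separate lines.

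On what is measured, Participant timeline {13} says "blood gas analysis including electrolytes will be performed at a minimum of once a day as long as the patient is in ICU/IMC" and "Serum osmolality and urinary sampling will be performed at hospital admission (day 1) and on days 3, 7, 10, at day 14". On entry, the inclusion criterion is "All adult patients suffering from non-traumatic SAH and admitted to the Intensive Care Unit (ICU) or Intermediate Care Unit" at a study centre, and the timeline adds "All eligible patients will be randomised within 24 h of diagnosis (time stamp on first computed tomography or MRI". Sodium disorder at entry is not among the exclusions.

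**The concern.** Sodium is unusual among the secondary endpoints. Mortality and length of stay have no starting value, and the article describes mRS, GOSE and miniMOCA only at day 90. Sodium is measured repeatedly, beginning close to randomisation, and the first value is likely to predict later ones. The covariate rule treats it like the rest.

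The endpoint also bears on the trial's reasoning. The hypothesis begins "We hypothesise that the use of a sodium-enriched solution (0.9% saline) for fluid therapy in patients with non-traumatic SAH", and the background names hyponatraemia as a contributor to vasospasm and says of it: "The latter is a common phenomenon in patients with SAH and occurs in 30 to 50% of the patients". If the primary result is null, readers will look at the sodium endpoints to see whether the two fluids led to different sodium. An analysis with less power than the data allow makes a null result there harder to interpret.

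What is at stake is efficiency. Randomisation balances starting sodium on average, so the site-only comparison is valid.

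**Working it through.** **Plan's own figure.** The article states no power, sample size or effect for the sodium endpoints, so there is nothing to reproduce. The 160 per group in Sample size {14} is for vasospasm and is used here only as the number of patients.

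**Inputs from the article.** 160 per group, 1:1; drop-out 15%, so 160 × 0.85 = 136 evaluable per group; alpha 0.05, taken here as two-sided; three sites; hyponatraemia in 30 to 50%.

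**Assumptions, not in the article.** Hyponatraemia of 40% in the Ringer's lactate arm (middle of 30 to 50%); about 27% in the saline arm; correlation rho between pre-fluid and later sodium on a latent normal scale, shown at 0.3, 0.5 and 0.7.

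**Step 1: power without the covariate, as an anchor.** With p̄ the mean of the two rates, power = Φ{[|p1 − p2|√n − 1.96√(2p̄(1 − p̄))] / √(p1(1 − p1) + p2(1 − p2))}.

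- n = 160, 40% v 27%: (0.13 × 12.649 − 1.96 × √0.4456) / √0.4371 = (1.644 − 1.308) / 0.661 = 0.508, so power is 0.69.
- n = 136, 40% v 26.3% (a latent shift of 0.38 SD: Φ(−0.253 − 0.38) = 0.263): (0.137 × 11.662 − 1.96 × √0.4433) / √0.434 = about 0.44, so power is 0.67.

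**Step 2: power with and without the covariate.** Each simulated trial was analysed by logistic regression with site only, and again with site plus pre-fluid sodium.

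| rho | 160 per arm, 40% v 27% (1,500 trials) | Gain (points) | 136 per arm, 40% v 26.3% (1,000 trials) | Gain (points) |
|---|---|---|---|---|
| 0.3 | 69.5% to 72.7% | 3.2 | 66.7% to 68.6% | 1.9 |
| 0.5 | 69.7% to 76.3% | 6.6 | 66.8% to 74.3% | 7.5 |
| 0.7 | 68.1% to 83.1% | 15.0 | 65.7% to 79.5% | 13.8 |

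The site-only columns agree with Step 1. The Monte Carlo standard error of a single power figure is about √(0.695 × 0.305 / 1500) = 1.2 points in the first set-up and √(0.667 × 0.333 / 1000) = 1.5 points in the second. The gain at rho 0.3 should therefore be read only as small.

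**Step 3: type I error.** With no treatment effect and 600 trials per setting, rejection lay between about 3% and 7% in both models, which is compatible with 5%.

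**Step 4: number of days.** In a linear model, adding a covariate with correlation r to the day count multiplies the residual variance by 1 − r²: 0.91, 0.75 and 0.51 at r = 0.3, 0.5 and 0.7. This r relates sodium to a count of days and need not equal the rho above.

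**What was not calculated.** Hypernatraemia: the article gives no rate for it.

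**The case against.** The strongest reply is that adjustment for the stratification factor alone is a legitimate prespecified analysis, that the secondary endpoints are exploratory with no power claimed, and that adding a prognostic covariate is a matter of preference. This stands as far as validity goes and sets the weight of the point: it is an improvement, not the correction of an error. It does not remove the point, because the article states the covariate set rather than leaving it open, and the stated set is less efficient than the data are likely to allow.

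Three further objections stand and limit what may be said.

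- **Carried-in disorder.** A reader might infer that, because the model holds site only, a patient already hypo- or hypernatraemic before study fluid is scored as an event. The documents do not support this. The article neither includes nor excludes such cases, and the full protocol or SAP may settle it. Nor does the inference follow: covariates do not decide what counts as an event, and adding baseline sodium would not change the count.
- **The pre-fluid value.** The article promises electrolytes at least daily in ICU/IMC, and serum osmolality and urine on day 1. It does not say that a sodium value precedes the first study fluid. Enrolment from ICU/IMC up to 24 h after diagnosis makes one likely, not certain.
- **Mechanism.** These endpoints are not the only evidence on sodium separation. Pre-planned substudies includes an analysis of electrolyte shifts over the active study phase. Hypertonic saline for low sodium is also permitted, which may narrow the contrast in threshold-based endpoints whatever the model.

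**Conclusion.** The point holds as a low-severity matter of efficiency. For the sodium endpoints, site-only adjustment probably leaves a useful predictor unused. Under the assumed rates the loss is negligible to small if first and later sodium are weakly correlated, and material only from a correlation of about 0.5 upward. The direction does not depend on the assumptions; the size does, and the article supplies neither the correlation nor the rates by arm.

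A stronger reading, that the sodium comparison is biased or its type I error inflated, is not supported: any imbalance in starting sodium is due to chance. In the logistic model the gain is in power, or in the precision of a standardised risk difference; the standard error of the log odds ratio itself does not shrink.

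**What to change.** In the statistical methods section {20a}, add one sentence: for the hyponatraemia and hypernatraemia endpoints (occurrence and number of days), the model includes trial site and, as a continuous covariate, the last sodium measured before the first study fluid. Model the two disorders separately, as Table 1 lists them; a single linear sodium term would not suit an endpoint that combines low and high values.

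State the rule for a missing pre-fluid value: a missing indicator, or single imputation of the baseline such as the overall mean. Do not use a value taken after study fluid started, because the fluid may already have changed it and adjustment could then remove part of the effect. The article's last-observation-carried-forward rule is for measurements after baseline and does not cover this.

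Since the plan reports risk differences and relative risks for dichotomous secondary outcomes, derive these from the adjusted model by standardisation; its odds ratio is conditional on starting sodium.

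Separately, confirm in the full protocol or SAP when counting starts and whether disorder already present before study fluid counts.

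The cost is a sentence or two and retrieval of a value that should usually be on file; some patients may lack one. No interim analysis is planned and the analysts are blinded, so the change can still be prespecified. The primary analysis does not change.

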## Assignment of interventions: allocation

### Sequence generation {16a}, concealment mechanism {16b}, and implementation {16c}

REDCap will be used to allocate eligible patients in a 1:1 ratio to either the normal saline group or the lactated Ringer’s group. Randomisation will be stratified by trial site. Dedicated and trained study personnel at all sites will enrol patients and subsequently inform the team of the patients’ allocation. A box with the blinded study fluids will be given to the treating intensive care physician with the patient’s study number. Study fluid will be blinded so that no identification of the study fluid will be possible by the treatment team. The randomisation list will be held by the study’s data manager (member of the CTU of the University of Bern). All patient data will be encoded using a code for each patient included in the study. Decoding will only be possible for the primary investigator of the study. No data on patients’ identity will be presented.

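### Hypo- and hypernatraemia are modelled with trial site as the only covariate; adding the last sodium before study fluid would gain precision at almost no cost

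*Protocol article*

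**What the plan says.** Statistical methods for primary and secondary outcomes {20a} names the models and their covariate: logistic regression for binary secondary endpoints and "linear regression models (such as mRS, GOSE, and miniMOCA) adjusted for the stratification variable (trial site"). The three scales in brackets are examples. The sentence covers the secondary endpoints as a whole.

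The Secondary endpoints section includes "occurrence of hyper- or hyponatraemia (proportion of patients and number of days with hyper- or hyponatraemia"), and Table 1 lists both disorders under electrolytes. Neither place gives a counting window or mentions the value at entry.

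On measurement, Participant timeline {13} says that "blood gas analysis including electrolytes will be performed at a minimum of once a day as long as the patient is in ICU/IMC". It also says "Serum osmolality and urinary sampling will be performed at hospital admission (day 1"), and "All eligible patients will be randomised within 24 h of diagnosis". On allocation, "Randomisation will be stratified by trial site", in a 1:1 ratio. On status, "Secondary outcomes will be analysed in an explorative way".

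**The concern.** A patient's sodium before treatment is a natural predictor of whether, and for how long, sodium is out of range afterwards. The 90-day scales have no such pre-treatment value; sodium does. A model with site alone leaves the variation explained by entry sodium in the residual error.

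Sodium also matters more here than an ordinary laboratory endpoint. Background and rationale {6a} names episodes of hyponatraemia among the contributors to vasospasm, and the Discussion offers stable sodium as a possible reason for benefit from saline. If the primary result is null, readers will ask whether the fluids changed sodium at all. If it is positive, they will ask whether sodium explains it. A needlessly imprecise sodium comparison answers both questions less well.

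**Working it through.** The article states no power or precision figure for the sodium endpoints, so there is none to reproduce.

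**Inputs from the article.** 160 patients per group and 15% drop-out (Sample size {14}), giving 160 × 0.85 = 136 evaluable per group, 272 in all. Hyponatraemia "occurs in 30 to 50% of the patients" (Background and rationale {6a}).

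**Assumptions.** Overall hyponatraemia of 40% in one arm (middle of that range); risk ratio 0.70 for new cases; 5 to 15% affected at entry; correlation ρ of 0.3, 0.5 or 0.7 between entry sodium and the outcome; two-sided 5% test.

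**Step 1. Is the covariate on file?** Electrolytes are measured at least daily in ICU/IMC, day-1 sampling takes place at hospital admission, and randomisation may follow the scan by up to 24 h. A sodium value before the first study fluid is therefore very likely. It remains an inference: the day-1 sampling names osmolality and urine, not serum sodium, and the SPIRIT table is not shown.

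**Step 2. Is there bias?** With no fluid effect, a share q affected at entry in both arms and 136 per arm, 200,000 simulated trials gave a mean risk difference of 0.000. Type I error was 5.3%, 5.2% and 4.8% for q = 5, 10 and 15%. The chance imbalance at entry has SD √(2q(1−q)/136) = 2.6, 3.6 and 4.3 percentage points. This is random error that the confidence interval already includes.

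**Step 3. Linear models.** Adjustment multiplies the SE by √(1−ρ²), and 272 patients then carry the information of 272/(1−ρ²). For number of days, ρ is the correlation of entry sodium with the day count.

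| ρ | SE factor | SE reduction | 272 act like |
|---|---|---|---|
| 0.3 | 0.954 | 5% | 299 |
| 0.5 | 0.866 | 13% | 363 |
| 0.7 | 0.714 | 29% | 533 |

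**Step 4. Logistic models.** Simulation with 3,000 trials per setting. Entry sodium and the later lowest sodium are bivariate normal with correlation ρ. 10% are affected at entry and counted as events, and site is omitted because it has no effect in the simulation.

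| Setting | ρ | Power without entry sodium | Power with it | Gain (points) |
|---|---|---|---|---|
| 136 per arm, 40% overall, new-case risk ratio 0.70 | 0.3 | 34% | 39% | 5 |
| | 0.5 | 35% | 42% | 8 |
| | 0.7 | 33% | 49% | 16 |
| 160 per arm, new cases 40% vs 28% | 0.3 | 49% | 56% | 7 |
| | 0.5 | 51% | 62% | 11 |
| | 0.7 | 50% | 70% | 20 |

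The gain is smaller if nobody counts as an event by entry status alone: with 136 per arm and 40% vs 28%, power was 57% to 59%, 56% to 63% and 57% to 71%. Type I error stayed at 5 to 6% with and without the covariate.

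**Step 5. What entry cases do to the contrast.** Take q = 10% and an overall rate of 40%. New cases in that arm are (0.40 − 0.10)/0.90 = 33.3%, and in the other arm 0.70 × 33.3% = 23.3%. The second arm's overall rate is 0.10 + 0.90 × 0.233 = 31%, so the observed risk ratio is 0.31/0.40 = 0.78. For q = 5, 10 and 15% it is 0.74, 0.78 and 0.81. Power with all 136 per arm is 44%, 34% and 25%. Restricting to unaffected patients (129, 122 and 116 per arm) gives 48%, 41% and 34%, a net gain of 4 to 9 points. The covariate restores precision but does not undo this dilution, and restriction undoes it only by dropping patients.

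**The case against.** The strongest reply is that a model adjusted for the stratification factor is valid, that these endpoints are exploratory, that the confirmatory question concerns vasospasm, and that electrolyte shifts are a separate pre-planned substudy. All of this is true, and it limits the severity. It does not remove the point: the article itself fixes the covariate set, so this is not a detail left open for the analysis plan, and the substudy's model is not described.

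A second reply is that the size of the gain rests on assumptions. That also stands. At a correlation of 0.3 the gain is modest, and no passage supports any particular value.

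Two stronger readings are tempting, and the documents support neither. A reader might infer that dysnatraemia present at entry is counted as an effect of the fluid. Under 1:1 randomisation such patients are expected equally in both arms; if counted, they pull the contrast towards no effect and add noise, but create no false one. A reader might also infer that the main endpoint must be limited to new cases. The article is silent on the counting window, which an article may leave to the full protocol or analysis plan. For number of days, patients out of range at entry carry information, since how long this lasts may depend on the fluid.

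**Conclusion.** The point holds as a loss of precision, not as a bias or an error in the test. Site is the only stated covariate for the sodium endpoints, and a strong candidate covariate is very likely recorded. Under the stated assumptions, adjustment shrinks the SE in linear models by about 5 to 29%. It adds roughly 5 to 20 points of logistic power when 10% are affected at entry and counted, and 2 to 14 points with 136 per arm when none count by entry status alone. The conclusion depends on a sodium value before study fluid being on file and on its correlation with the outcome; the direction was the same in every setting tried. Severity is minor.

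**What to change.** In Statistical methods {20a}, state that the hypo- and hypernatraemia models, for both occurrence and number of days, are adjusted for trial site and for the last recorded sodium before the first study fluid, entered as a continuous covariate. Keep all patients in the main analysis. Because the article promises risk differences and risk ratios, obtain them from the adjusted logistic model by averaging predicted risks over all patients, so that the reported measure stays the same. As a sensitivity analysis, report occurrence among patients whose sodium was within the normal range at entry.

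The cost is a few lines of analysis-plan wording, one derived variable and a rule for patients with no value before study fluid. If the inference about availability is right, no new sampling is needed; this should be confirmed in the database first. No interim analysis is planned and data analysts are blinded, so the change can still be prespecified cleanly.

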**Table 2 Tab2:**
[figure not shown]
SPIRIT figure

Neurological outcome will be assessed by the modified Rankin Scale (mRS), Glasgow Outcome Scale Extended (GOSE), and Montreal Cognitive Assessment (miniMOCA) at day 90 (see Supplementary Figures S1–S3). Mortality will be assessed at day 30 and 90.

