### Recruitment {15}

All centres will perform daily screening of all ICU admissions in order to secure adequate recruitment. Recruitment of study participants will be reported to the trial sponsor and lead principal investigator via automated alert system in REDCap. Patients with SAH are critically ill and a vast majority of patients stay on the ICU or IMC for 14 days after the diagnosis; thus, loss of follow-up or other events are unlikely to interfere with the primary outcome. In addition, patients with SAH are treated in dedicated centres and—as part of their routine management—are being followed up by the neurosurgical team. Thus, we expect to gain information about their neurological outcome from a majority of our enrolled patients.

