## Data collection and management

### Plans for assessment and collection of outcomes {18a} and plans to promote participant retention and complete follow-up {18b}, and data management {19}

Data will be obtained from the participant’s hospital files, study-specific examinations (e.g. bioimpedance results), the Insel Data Science Centre (IDSC) and national registries (mortality data) and by participant survey/interview and entered in the web-based eCRF (REDCap) by authorised trial personnel. For participants transferred from a trial ICU to a non-trial ICU, data related to the outcomes will be collected according to investigator contact with the non-trial ICU.

Long-term disability will be assessed by telephone interview or at the outpatient clinic appointment in the neurosurgical unit based on the modified the mRS, GOSE, and miniMOCA (see Figures S1–S3 in the Supplemental File for more details).

All data will be verified by regular monitoring, as well as data validity checks and automated consistency queries in the trial database. A final data quality check will be performed before the database is closed. All data changes and checks are tracked in the database.

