### Methods in analysis to handle protocol non-adherence and any statistical methods to handle missing data {20c}

A logistic regression analysis in the per protocol population adjusted for the stratification variable (trial site) is planned. Missing data is handled by the last observation carried forward method. In case the number of drop-outs exceeds the expected rate of 15%, the excess drop-outs will be replaced by recruitment of new subjects.

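### LOCF is the only imputation method named, but it cannot fill a missing day-90 scale, and it scores patients of unknown vital status as alive

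*Protocol article*

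**What the plan says.** Section {20a} of the protocol article sets the rule: "Missing values will be imputed with the use of the last-observation-carried-forward method for measurements made after baseline". Section {20c}, which is devoted to non-adherence and missing data, repeats it without the restriction to post-baseline measurements: "Missing data is handled by the last observation carried forward method". Neither section exempts an outcome or names another imputation method.

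The schedule for the functional and cognitive scales is in the text beside Table 2: "Neurological outcome will be assessed by the modified Rankin Scale (mRS), Glasgow Outcome Scale Extended (GOSE), and Montreal Cognitive Assessment (miniMOCA) at day 90". Outcomes {12} and Table 1 also place them at day 90. On how they are collected, the data-collection section says: "Long-term disability will be assessed by telephone interview or at the outpatient clinic appointment in the neurosurgical unit". On completeness, Recruitment {15} says: "Thus, we expect to gain information about their neurological outcome from a majority of our enrolled patients".

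For death, "Mortality will be assessed at day 30 and 90", and the data-collection section lists national registries as a source of mortality data.

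The primary endpoint has its own rule in {20a}: "deceased patients or patients who were transferred prior to reaching the primary endpoint will be counted as" no event.

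**The concern.** LOCF needs an earlier measurement of the same variable. For the three day-90 scales the text gives none, so the prescribed method cannot be carried out on the outcomes for which missing values are most plausible. They depend on a telephone call or clinic visit, and the article gives no expected completeness beyond a majority.

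For 90-day mortality an earlier value does exist, and for any patient with unknown later status that value is alive. Carrying it forward asserts survival that nobody observed.

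The abstract lists mortality and 90-day neurological outcome among the key secondary outcomes. A rule that is impossible for one and one-sided for the other leaves the real analysis to be settled after the data are in.

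**Working it through.** The plan gives no figure on this point, so there is nothing to reproduce. The check sets the rule beside the schedule and then sizes the mortality effect under stated assumptions.

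**1. Day-90 scales**

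- Rule: carry the last post-baseline value forward ({20a}, {20c}).
- Schedule: mRS, GOSE and miniMOCA at day 90 (Outcomes {12}, Table 1, text beside Table 2). The data-collection section describes no earlier assessment.
- Analysis: linear regression adjusted for trial site ({20a}), which needs a day-90 value for every patient included.

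The number of earlier values is zero, so LOCF supplies nothing. A patient with a missing scale falls out of the regression. The resulting complete-case analysis is unbiased only if, given arm and site, missingness is unrelated to the outcome. The plan neither states nor defends that condition, because it says the values will be imputed.

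The SPIRIT schedule (Table 2) is a figure that could not be read. If it contains an earlier mRS or GOSE, LOCF becomes possible but holds a recovering patient at an early value. That is a different defect and does not rescue the rule.

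**2. 90-day mortality**

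Inputs:

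- N = 160 per arm (Sample size {14}), used only to convert percentages to counts.
- L = share of the arm last known alive whose day-90 status stays unknown after registry linkage. Not in the documents; assumed 5% to 15%.
- r = risk of death by day 90 among those patients. Not in the documents; assumed 5% to 20%.

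LOCF scores all N × L of these patients as survivors. Deaths missed per arm = N × L × r. Understatement in percentage points = 100 × L × r.

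| L | r | Deaths missed per arm | Understatement (points) |
|---|---|---|---|
| 5% | 5% | 160 × 0.05 × 0.05 = 0.4 | 0.25 |
| 5% | 20% | 160 × 0.05 × 0.20 = 1.6 | 1.0 |
| 15% | 5% | 160 × 0.15 × 0.05 = 1.2 | 0.75 |
| 15% | 20% | 160 × 0.15 × 0.20 = 4.8 | 3.0 |

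The error has one sign only. It is zero if L = 0, that is, if linkage is complete.

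**3. Effect on the comparison**

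The risk difference shifts by the difference between the arms in L × r. With equal L and r the shift is zero. With 5% unknown in one arm, 15% in the other and the same r, it is (0.15 − 0.05) × r. That is 0.5 points at r = 5% and 2.0 points at r = 20%, in favour of the arm with more loss.

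**The case against.** The strongest reply is that the article condenses a longer protocol, that imputation detail belongs in an SAP, and that little is at risk. Secondary outcomes are exploratory, registries should make unknown vital status rare, and the arms are blinded, so differential loss is not expected.

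The first part fails. The article does not leave the method open. It fixes one, twice, and an SAP would have to follow or contradict it. The rest stands and limits the size of the point: the mortality effect may be near zero, and equal loss largely cancels in the contrast. Neither helps the day-90 scales, where the rule cannot be carried out at all.

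A reader might infer four stronger claims that the documents do not support:

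- **LOCF biases the primary endpoint by carrying lost patients as free of vasospasm.** Deaths and transfers before the event are classified by the separate rule in {20a}, not by LOCF. That section also plans a composite sensitivity analysis that counts death and readmission for vasospasm within 14 days. The data-collection section provides for outcome data from non-trial ICUs after transfer.
- **LOCF inflates days with abnormal sodium.** It repeats whatever came last. An abnormal value adds such days and a normal one removes them, so the direction is unknown. Participant timeline {13} also requires electrolytes at least daily in ICU/IMC, so gaps should be few.
- **The plan expects 15% of day-90 values to be missing.** The 15% in {14} is a drop-out allowance in the sample size for the vasospasm endpoint. No day-90 loss rate is stated. The upper value of L above is an assumption and not that figure.
- **Confidence intervals for the day-90 scales will be too narrow.** That follows from treating imputed values as observed. Where LOCF cannot run, nothing is imputed.

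**Conclusion.** The point holds in a limited form. As written, LOCF cannot supply a missing mRS, GOSE or miniMOCA, so the stated analysis cannot be performed and an undeclared complete-case analysis takes its place. This rests on the readable text, because the SPIRIT figure is not shown.

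For 90-day mortality the rule is one-sided. It lowers mortality by 0.25 to 3.0 points per arm under the assumed ranges, by much less if linkage is near complete, and it moves the contrast mainly when loss differs between arms (0.5 to 2.0 points for 5% against 15%).

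The primary analysis is not shown to be affected. The outcomes concerned are exploratory, so this is a change that should be made and not one on which the trial's main conclusion depends.

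**What to change.** Delete LOCF from {20a} and {20c} and put in its place:

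- **Day-90 scales in survivors:** multiple imputation under missing at random, with arm, site and the baseline and in-hospital predictors already collected. Add a delta-adjusted or best/worst-case sensitivity analysis for departures from that assumption.
- **Deaths:** since imputation is confined to survivors, state how deaths are scored on the mRS and GOSE.
- **90-day mortality:** take vital status from the national registries already named. If it is still unknown, censor at last contact instead of recording survival.

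The cost is revised wording in two sections and a standard imputation run on exploratory secondary outcomes, with no new data source. At the time of the article 157 patients (49%) had been randomised, no interim analysis was planned and data analysts were to be blinded. The change can therefore be made without knowledge of results.
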